### Methods in analysis to handle protocol non-adherence and any statistical methods to handle missing data {20c}

Missing data will be explored. Imputation of missing values is not planned in order to analyze “real-life” data.

### Plans to give access to the full protocol, participant-level data, and statistical code {31c}

The present protocol article will be the only one to be published. This article and supplementary material (randomization script) will be made available on an open access platform (e.g., SportRxiv, HAL).

At the end of the study, we will do the same with the article presenting the results, the participants data (which will stay pseudonymized and will not have any sociodemographic information), and the analyses scripts.

## Oversight and monitoring

### Composition of the coordinating center and trial steering committee {5d}

The principal investigator and post-doctoral fellow will be responsible for the design, planning, and conduct of the study, informing the other partners of their missions, preparing the protocol and documents (flyers, questionnaires, consent form, ethics committee application) and their revisions, organizing steering committee meetings, being in charge of the first videoconference to explain the study in detail to each participant and randomization and the collection of signed consent forms, and directing the valorization of results (reports, articles). They will also report any adverse events to the Data Protection Committee.

The principal investigator, the post-doctoral fellow, and two biostatisticians will collect, verify, and analyze the data. In each health center, specialists will provide information about the study to their patients when they meet the inclusion/exclusion criteria. They will also be part of the study’s steering committee, which thus includes gynecological surgeons, endometriosis experts, pain specialists, and APA experts, and will schedule periodic (every 3 months) meetings to first validate the protocol and then review the study’s progress and discuss solutions to overcome any problems or obstacles identified. These people are not part of the sponsor’s services and have no competing interests.

### Composition of the data monitoring committee, its role and reporting structure {21a}

The present study can be acknowledged as a minimal risk study. The data monitoring committee includes two biostatisticians, one endometriosis specialist, and one APA specialist. Even if they will also be part of the steering committee, their role is distant enough from the study to ensure their impartiality. They will meet twice a year, starting with 1 month after the start of the recruitment, and will evaluate the trial data for patient safety, study conduct, and progress and will make recommendations to the steering committee to improve the study. They are not part of the sponsor’s services and have no competing interests.

### Adverse event reporting and harms {22}

Endometriosis specialists and APA teachers will monitor and collect adverse events related or not to the treatment proposed in the study. Also, any detrimental event occurring during the study (e.g., worsening of pain, injury) will be considered as adverse events. These events will be reported to the person protection committee [comité de protection des personnes, CPP].

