### Description of the “APA” arm

In addition to PA recommendations, participants randomized to this arm will receive PA sessions via videoconference for 6 months. The sessions will be based on the personalized PA assessment and will last between 45 min (at the beginning of the program) and 1 h, 1 to 3 times a week, supervised or on their own. Participants will benefit from this program free of charge (Table 1).

**Table 1 Tab1:** Duration and type of PA proposed

Physical activity	Month #1	Month #2	Month #3	Month #4	Month #5	Month #6
Pilates/stretching/yoga Intensity: light to moderate *Sessions with APA teacher*	45 min	45 min	60 min	60 min	60 min	60 min
Cardio fitness Intensity: light *Sessions with APA teacher*			60 min	60 min		
Cardio Intensity: light to moderate *Sessions with APA teacher*					60 min	60 min
Pilates/stretching/yoga + cardio fitness Intensity: light to moderate *Autonomous sessions*				Duration decided by participants		
Total duration of PA from the study	45 min	45 min	120 min	> 120 min	> 120 min	> 120 min

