#### Structured sessions

Each session will include the following:A warm-up periodStretching, yoga, Pilates, or endurance during the cardio fitness sessions (light to moderate)A recovery period consisting of stretching and relaxation

The duration and intensity of the sessions will be modified according to the physical evaluation and the patients’ declarations at the beginning of each session. In case of intense fatigue and pain, the sessions will be adapted.

The duration and the intensity of the sessions will also evolve according to the capacities of the patients evaluated in a declarative way at the end of each realized session: pain, fatigue, and quality of life.

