### Recruitment {15}

Participants will be recruited online via social media, printed media, radio, and patient associations as well as through the endometriosis specialists who are part of the study. Patients will receive a flyer, and those interested in participating will receive a link, QR code, and the email address of the principal investigator to be able to demonstrate his/her interest.

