## Data collection and management

### Plans for assessment and collection of outcomes {18a}

Variables will be assessed (1) online via self-report measures and (2) via the questionnaire proposed by the APA teacher at the beginning and at the end of the APA sessions. Primary outcomes will be assessed at baseline, 3 months, 6 months (end of the study), and at 3 and 6 months’ follow-up for all arms. Secondary outcomes will be assessed at baseline, 6 months (end of the study), and 6 months’ follow-up. Sociodemographic variables will be assessed at baseline only.

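### Adverse events are collected through staff whose contact differs by arm, so crude between-arm counts of non-serious events would be biased; two sections also name different recipients for the reports

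*Protocol article*

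**What the plan says.** Under Adverse event reporting and harms {22}, the protocol article names two groups of collectors: "Endometriosis specialists and APA teachers will monitor and collect adverse events related or not to the treatment proposed in the study". The definition is broad: "any detrimental event occurring during the study (e.g., worsening of pain, injury) will be considered as adverse events".

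Contact with these collectors is set elsewhere in the article:

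- **APA arms.** Sessions run "1 to 3 times a week, supervised or on their own" for six months. Under Plans for assessment and collection of outcomes {18a}, some variables are gathered "via the questionnaire proposed by the APA teacher at the beginning and at the end of the APA sessions". Under Structured sessions, patients' capacities are "evaluated in a declarative way at the end of each realized session: pain, fatigue, and quality of life", so that later sessions can be adapted.
- **Education arm.** Twelve one-hour sessions over six months, some with the principal investigator and some with an endometriosis specialist.
- **Waitlist arm.** A booklet and a video only, until the programme is offered after six months.
- **All arms.** One physical assessment by an APA teacher at inclusion and a second assessment at six months. Online questionnaires, including the pain and fatigue scales, at baseline, 3 and 6 months, and 3 and 6 months after the intervention.

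On recruitment: "Participants will be recruited online via social media, printed media, radio, and patient associations", as well as through the study's specialists.

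On who receives the reports, the section on the coordinating centre {5d} says of the principal investigator and post-doctoral fellow: "They will also report any adverse events to the Data Protection Committee". Section {22} says: "These events will be reported to the person protection committee" (the CPP).

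**The concern.** How many injuries or pain flares are recorded depends on how often someone in a position to record them meets the participant. One of the two named collector groups, the APA teachers, sees the APA arms week after week and the other two arms only at the assessments. The other group, the specialists, has no stated schedule of enquiry and may not reach everyone. Recruitment runs through media and associations and extends to several French-speaking countries, while the partner centres listed under informed consent {26a} are French.

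Two things are at stake. A table of adverse events by arm could show more events with exercise when there is no true difference. Events in the waitlist arm could also go unrecorded, which weakens the background against which the data monitoring committee judges safety. Separately, a reader cannot tell from the article which body receives adverse-event reports.

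**Working it through.** The article gives no adverse-event rate and no harms calculation, so there is no figure to reproduce. The check counts scheduled contacts and then illustrates what unequal detection can do.

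**Step 1: scheduled contacts in six months.** Inputs are Table 1 (one supervised session type in months 1–2, two in months 3–6), the two assessments in Intervention description {11a}, and the 12 education sessions. Each Table 1 entry is read as one session a week, which fits the abstract's range of 45 to more than 120 minutes a week. Full attendance is assumed, with 52/12 = 4.33 weeks per month.

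Supervised sessions = 2 × 4.33 × 1 + 4 × 4.33 × 2 = 8.7 + 34.7 = 43.3. With four-week months the count is 8 + 32 = 40.

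| Arm | Supervised APA sessions | Assessments | APA-teacher contacts | Education sessions | All scheduled contacts |
|---|---|---|---|---|---|
| APA | 43 | 2 | 45 | 0 | 45 |
| APA + education | 43 | 2 | 45 | 12 | 57 |
| Education | 0 | 2 | 2 | 12 | 14 |
| Waitlist | 0 | 2 | 2 | 0 | 2 |

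On the text's own range of one to three sessions a week, there are 26 × 1 = 26 to 26 × 3 = 78 sessions, some possibly unsupervised. The 45 is a central reading, not a fixed figure.

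**Step 2: effect of unequal detection (illustration).** Recorded proportion = true proportion × probability of detection. Assume that 30% of participants in both arms truly have a non-serious event. With 200 participants allocated 1:1:1:1 there are 50 per arm. The last column is the chance that a two-sided 5% comparison would show a significant excess in the APA arm:

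Φ[(Δ − 1.96 × SE₀) / SE₁], with SE₀ from the pooled proportion and SE₁ from the separate proportions.

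For 27% v 15%:
- SE₀ = √(2 × 0.21 × 0.79 / 50) = 0.0815
- SE₁ = √((0.27 × 0.73 + 0.15 × 0.85) / 50) = 0.0806
- (0.12 − 0.1597) / 0.0806 = −0.49, so the chance is 31%.

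| Detection, APA v comparator (assumed) | Recorded | Ratio | Chance of a false excess |
|---|---|---|---|
| 90% v 90% | 27% v 27% | 1.0 | 2.5% |
| 90% v 70% | 27% v 21% | 1.29 | 10% |
| 90% v 50% | 27% v 15% | 1.80 | 31% |
| 90% v 30% | 27% v 9% | 3.0 | 65% |

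With true proportions from 20% to 50%, the chance in the three unequal rows runs from 8% to 92%. This spread shows that the size cannot be fixed from the article; the direction follows from the contact pattern.

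**Step 3: the reporting line.** Section {5d} sends adverse events to a Data Protection Committee and section {22} to the CPP. The section on the data monitoring committee {21a} gives safety review to a third body. The text does not say whether the first name is a slip or a second recipient.

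**The case against.** The strongest reply is that no between-arm harms analysis is planned. Adverse events are not among the listed outcomes, the article calls the study minimal risk, and collecting events through the staff who see participants is ordinary safety surveillance. Forms and question wording also commonly sit in a fuller document. This stands in part: the absence of a form or schedule is not the point. The point is that the article itself fixes collectors whose contact differs by arm, and any tabulation of events by arm would inherit that.

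A reader might infer that APA participants are asked about adverse events at every session and the other arms hardly at all. The documents do not support this. The session questions concern pain, fatigue and quality of life, serve to adapt sessions, and are not described as adverse-event enquiry. No scheduled adverse-event enquiry is stated for any arm. The education arm has 12 sessions, some with a specialist. Usual care continues in all arms, and patients may contact the principal investigator at any time. There is also telephone or email follow-up at months 1, 2, 4 and 5, though its purpose is programme implementation and the arms it covers are unclear. The sharp contrast is with the waitlist arm.

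Pain is measured on the same scales at the same times in all arms, so worsening of pain can be compared without this bias. That narrows the problem to injuries, other non-serious events, and pain worsening taken from staff reports. On the reporting line, the two sections could describe two recipients, but neither says so.

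**Conclusion.** The concern holds in a limited form. Adverse-event ascertainment is unequal by arm: about 45 APA-teacher contacts in the APA arms against 2 in the waitlist and education arms, assuming Table 1 is weekly and attendance is full. Crude between-arm counts of non-serious events would tend to be inflated in the APA arms, and waitlist events may be missed. The size is unknown, because it rests on detection rates the article does not give; the ratios of 1.29 to 3.0 above are illustrations from assumed rates.

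It would go too far to call the harms comparison invalid. No formal comparison is announced, serious events depend less on routine contact, and pain already has a common measurement. The conflict over the receiving body needs no assumption: the two sections differ and must be reconciled.

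**What to change.** 1. Add the same short adverse-event items (injury, unplanned care, hospitalisation) to the online questionnaires that all arms already complete at 3 and 6 months and at both follow-ups.
2. Use the existing all-arm pain scales for worsening of pain, without adding a further item.
3. Base any between-arm harms summary on these common data, and report events collected at sessions separately for the APA arms. After six months the waitlist is due to receive the programme, so follow-up data should be labelled accordingly.
4. Reconcile {5d} and {22} on who receives adverse events.

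The cost is a few extra online items and slight questionnaire burden, plus one clarifying line on reporting. No treatment rule changes, and event capture in the waitlist arm improves.

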### Frequency and plans for auditing trial conduct {23}

The trial will be monitored by the principal investigator. The CPP could conduct additional independent auditing.

### Plans for communicating important protocol amendments to relevant parties (e.g., trial participants, ethical committees) {25}

The CPP will be notified for approval of any protocol modifications. Updates of the protocol would be done.

### Dissemination plans {31a}

Trial results will be communicated via articles in scientific journals, on open access and pre-print platforms, on public media, in oral communication during conferences, in patient’s association seminars, and to patients via a report which will be also sent to sponsors.

## Discussion

The aim of the study will be to test the effect of APA and/or endometriosis-based education to reduce pain and fatigue and to increase PA in patients with endometriosis. Given the limited effectiveness of current treatment (pharmaceutical treatment and surgery), in order to find a way to help improving the effectiveness of the treatment particularly on QoL, there is a need for assessing the efficacy of non-medical interventions targeting physical and mental health via a relatively low-cost solution: PA. The objective is not to replace current treatment but to include in the treatment protocol non-intervention which could improve QoL. In order to investigate the effectiveness of the intervention, a waitlist control will be recruited and used as the comparator. It was expected that the combined intervention will have more important effect than other interventions and the control group. The separate interventions (i.e., only APA, only endometriosis-based education) are supposed to be equivalent not only for QoL but also for pain and fatigue, but the APA intervention is supposed to increase PA during and after the intervention, regarding the content of the intervention.

If several strengths of this study could be highlighted, some limitations should be also considered. Investigating four arms this study will inform about the effectiveness of the two-intervention components separately and combined. The sample size will be large enough to obtain reliable results. The videoconference modality will ease the recruitment and the adherence for PA sessions. Study about endometriosis and PA are scarce, and this study will help to partly fill this scientific gap.

The use of video of movement and waiting list could result in a Hawthorne effect. However, to control this effect, the same video will be sent to every participant, and the duration of the study should be sufficient to decrease this potential effect. Otherwise, it seems more ethical to propose to participants in the control group to also benefit from a potentially effective treatment. The videoconference modality and online questionnaire induce a selection bias given that only patients with electronic device, numerical literacy, and Internet access will be able to participate. However, if the program is proven to be effective, it could be easily adapted for an on-site intervention.

## Conclusion

Results from the present study will help to improve care for persons who suffer from endometriosis by informing health professionals about the effectiveness of PA and education to reduce the symptoms and by giving some guidelines and advices to do so.

## Trial status

The trial is registered; trial registration: ClinicalTrials.gov, NCT05831735. Date of registration: April 25, 2023. Recruitment will start in March 2023 and will be completed in December 2024. The current protocol is version 1 (dated April 25, 2023).

## Abbreviations

APA: Adapted physical activity
CPP: [Comité de protection des personnes]
EHP-30 + 23: Endometriosis Health Profile 30 + 23
PA: Physical activity
PI: Principal investigator
QoL: Quality of life
